#### Time-intensive CBT

This will comprise 8–10 h (depending on the disorder) of one-to-one CBT delivered in 4–5 sessions over 1–2 weeks, delivered at the earliest convenient point between 12 and 36 weeks of pregnancy. The CBT treatment will be delivered by a high-intensity cognitive behaviour (HI CBT) therapist, which is standard practice within IAPT services. Two follow up sessions of 1 h each will then be offered by the HI CBT therapist which will include one in late pregnancy (33–35 weeks’ gestation) and one at 1m postpartum.

#### Standard weekly CBT (treatment as usual)

Standard weekly CBT will comprise 8–10 hours (depending on the disorder) of one to one CBT on a one hour per week basis. This is termed ‘high intensity’ CBT in IAPT services and will be offered to all women who participate in the trial and are randomised to standard weekly CBT. The CBT treatment will be delivered by a High Intensity Cognitive Behaviour (HI CBT) Therapist, which is standard practice within IAPT services. Two follow up sessions of one hour will then be offered by the HI CBT Therapist which will include one in late pregnancy (33–35 weeks’ gestation), one at 1m postpartum.

Treatments may take place via phone or video link using Microsoft Teams, depending on current restrictions due to the Coronavirus.

### Provisions for post-trial care

Women requiring and wishing for further intervention after the end of the trial will be referred or signposted to an appropriate intervention. This may be for further psychological therapy within IAPT or within more specialised perinatal mental health services.

### Criteria for discontinuing or modifying allocated interventions

Adverse events will be monitored and recorded including the mental and physical health of the mother and any pregnancy-related events. Should participants deteriorate clinically in terms of significantly increased symptoms of anxiety or depression, or an increase in risk to themselves or others, then the intervention will be stopped and a referral made to specialist perinatal services and/or other services as clinically appropriate.

### Strategies to improve adherence to interventions

Fidelity will be defined as delivering all key treatment components during treatment and will be established by a checklist of key components of treatment derived from core competencies for specific disorders using treatment notes [23]. This will be completed by the therapist at the end of each session. Standardised therapy note sheets will be kept and checked to establish fidelity against the checklist. Therapists will also be required to submit a random selection of therapy recordings to be rated for fidelity to CBT on an established scale, the Cognitive Therapy Rating Scale (CTS-R).

Client engagement and adherence to therapy will be rated by therapist at each session on a 4-point Likert scale, number of sessions attended will be recorded and the participants’ perspective will be assessed in detail in a qualitative interview at 3 months.

### Outcome progression criteria

Primary feasibility outcomes:
(i)if it is possible to identify/recruit patients via (a) information provided in healthcare settings at booking visits/by midwives/self-referral and (b) approach by a primary care therapist. We require a minimum of 30% of those approached to be eligible participants from each recruitment method for each to be deemed feasible. An acceptable recruitment rate (number of consented participants) would be at least 3 participants/month(ii)If participants are willing to be randomised. We require that 70% of eligible participants are randomised to be deemed feasible(iii)If the intervention is received as intended in both arms using a fidelity content checklist. A minimum of 70% of participants in the trial would need to complete > 60% of each intervention in hours for each to be deemed feasible, i.e. 7.2 h out of 12 [28]. For completers in the intensive arm, these treatment hours will need to be completed in the 2-week window(iv)Acceptability of both interventions to participants will be determined by qualitative investigation enquiring about experiences and positive and any negative effects of all aspects of treatment, and a 3-point rating scale to assess how useful the treatment was for anxiety and parenting(v)Establishing the parameters needed in order to estimate the sample size for a full trial. For example, standard deviation of the potential primary outcome measure GAD-7(vi)Participation and data completion at 3m outcome assessment; a follow up rate of > 70% is required to determine feasibility(vii)The acceptability of assessment measures to participants; this will be determined by qualitative interview and brief 3-point rating scales asking if it was acceptable and clear

Secondary clinical outcome measures:
(i)Clinical outcome measures for depression, anxiety, overall functioning and anxiety disorder symptoms collected at 3 months postpartum(ii)Health service use at 3 months postpartum

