Psychological treatments for anxiety disorders, primarily cognitive behaviour therapy (CBT), have a substantial evidence base [21–23]. Women are usually offered one-to-one disorder specific CBT based on best available evidence [24]. Individual CBT is ‘semi-idiographic’, that is, based on shared principles but tailored to the individual context and needs of the client. Modifications may be made according to the client’s physical state, such as not running upstairs in a panic exposure exercise if the person is unable, instead identifying other means to test relevant beliefs. Such modifications in pregnancy have been suggested and there is some evidence for the use of exposure-based CBT during pregnancy.

CBT is usually delivered in approximately 12-h-long weekly sessions, depending on the presenting disorder. Time-intensive CBT treatments (IN-CBT) have been trialled in (non-perinatal) patients with OCD, PTSD, social phobia and panic disorder with equivalent outcomes to standard weekly treatments, achieved in a much shorter time frame of 1 to 2 weeks [25–28]. This format has been found acceptable to patients. IN-CBT for postpartum OCD has been found to be safe and effective in the reduction of maternal OCD symptoms and acceptable to mothers [29, 30]. Given the clear aim of delivering fast and effective treatment, ideally before the baby is born, IN-CBT could be a helpful modification to traditional weekly CBT for pregnant women with anxiety disorders and may be more beneficial in terms of longer-term outcomes. Specific evidence is therefore needed to establish whether IN-CBT approaches are acceptable, produce equivalent engagement and adherence with treatment during pregnancy, are efficacious during pregnancy and helpful for maternal symptoms and parenting in the postpartum.

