### Inclusion criteria

Women must have the following characteristics prior to randomisation:
Aged ≥ 18 yearsPregnant, between 12 and 25 weeks gestationMeet criteria for Diagnostic and Statistical Manual of Mental Disorders Fifth Edition (DSM-V) for OCD, PTSD, social anxiety or panic disorder on the Structured Clinical Interview DSM-V (SCID-V)Eligible for referral to Lambeth, Lewisham, Southwark or Croydon IAPT services (i.e. has local general practitioner, common mental disorder and level of risk manageable within primary care)Available (by self-report) for either IN-CBT or standard weekly treatmentNot taking psychotropic medication or taking stable dose of medication for at least 6 weeksAble to provide informed consent

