### Statistical methods

#### Quantitative data

Quantitative data analysis will be primarily descriptive to aid the planning of a future RCT. Participant flow through the study will be presented following CONSORT guidelines. Descriptive data will be presented in the form of means and standard deviations; medians and ranges; or percentages with 95% confidence intervals, as appropriate depending on the data being described.

The following feasibility parameters will be calculated: (1) percentage of participants meeting eligibility criteria (those eligible/those approached or referred) by recruitment channel into the study; (2) number of participants recruited per month (defined as those consented); (3) percentage of individuals consenting to randomisation (those randomised/those consented); (4) percentage of participants completing treatment in each arm (number of participants receiving adequate treatment dose, defined as 60% of treatment hours/those randomised); (5) percentage completing the outcome measures at 3m postpartum (number of participants completed at least one follow-up measure/those randomised); (6) between group pre-post effect sizes and confidence intervals, adjusting for randomisation stratifiers (fixed effect) and therapist (random effect), and variance on the potential primary outcome measure at 3 months post-randomisation; (7) summary statistics on acceptability of intervention and outcome measures measured using a 3-point Likert scale. Data will be presented overall and subgroup summaries by disorder.

Descriptive data on therapist competence and compliance will be presented using standardised Cognitive Therapy Scale Ratings (CTS-R) and number of treatment elements completed from checklist.

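### Criterion (iii) takes 60% of 12 h, but only 8–10 h are planned in the intensive arm's 2-week window, so the effective bar is 72–75% of the course (90% for an 8 h course if 7.2 h is a fixed floor)

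*Protocol article*

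**What the plan says.** Outcome progression criteria (iii) asks that at least 70% of participants complete more than 60% of each intervention in hours. It gives the figure as "i.e. 7.2 h out of 12 [28]. For completers in the intensive arm, these treatment hours will need to be completed in the 2-week" window.

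The course itself is shorter than 12 h. On the intensive arm, the section Time-intensive CBT says: "This will comprise 8–10 h (depending on the disorder) of one-to-one CBT delivered in 4–5 sessions over 1–2 weeks". It adds: "Two follow up sessions of 1 h each will then be offered by the HI CBT therapist", one at 33–35 weeks of gestation and one a month after birth. The weekly arm has the same core hours and the same follow-ups: "Standard weekly CBT will comprise 8–10 hours (depending on the disorder) of one to one CBT on a one hour per week basis". It has no time window.

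On timing, women enter "between 12 and 25 weeks" of gestation, and the intensive course is "delivered at the earliest convenient point between 12 and 36 weeks of pregnancy".

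Parameter (4) under Statistical methods, Quantitative data, counts the "number of participants receiving adequate treatment dose, defined as 60% of treatment hours/those randomised". It does not say which hours form the base, does not mention the window, and has no 'more than' sign.

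**The concern.** The hours counted in the base are not all available in the window in which the intensive arm must earn them. A base of 12 h can be built from this trial's own interventions only as a 10 h course plus two 1 h follow-ups, and those follow-ups normally come weeks or months after the 2-week course. A rule described as more than 60% is then stricter than that for the intensive arm.

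This is a go/no-go threshold, applied to each format separately. If the base does not fit the course, a woman who received three quarters of her planned intensive CBT on time can be recorded as a non-completer. The two formats may also be judged on different amounts of core therapy. Because parameter (4) leaves the base open, two analysts could classify the same woman differently.

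**Working it through.** **The plan's own figure.** 0.60 × 12 h = 7.2 h, so the stated number is reproduced. The protocol does not say where the 12 h comes from. Two readings are possible:

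- 10 h core + 2 × 1 h follow-up = 12 h, in which case 7.2 h is a worked example for the longest course;
- the usual course described in the Background ("CBT is usually delivered in approximately 12-h-long weekly sessions"), in which case 7.2 h is a fixed floor taken from a course that this trial does not give.

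**Can the follow-ups fall in the window?** Latest entry is week 25 and the earliest follow-up is week 33, so 33 − 25 = 8 weeks lie between them. A 2-week window reaches week 33 only if it starts at week 31 or later. The second follow-up is after birth. Normally neither hour is available in the window.

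**Effective bar in the intensive arm** = required hours ÷ core hours planned in the window.

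| Core course | Scaled rule: 60% of (course + 2 h) | Share of course | Fixed floor | Share of course |
|---|---|---|---|---|
| 10 h | 0.6 × 12 = 7.2 h | 72% | 7.2 h | 72% |
| 9 h | 0.6 × 11 = 6.6 h | 73% | 7.2 h | 80% |
| 8 h | 0.6 × 10 = 6.0 h | 75% | 7.2 h | 90% |

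No row gives 60%. In a late start with the 33–35 week session inside the window, 1 h of the bar can come from that session. The core share needed is then (7.2 − 1)/10 = 62% for 10 h, and for 8 h (6.0 − 1)/8 = 62.5% scaled or (7.2 − 1)/8 = 77.5% fixed. Measured against core plus that one session, the bar is 7.2/11 = 65%, 6.0/9 = 67% and 7.2/9 = 80%. All remain above 60%.

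**Whole sessions, intensive arm.** The assumption is 2 h per session, inferred from 8–10 h in 4–5 sessions. There is no late start.

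- 10 h course: 3 sessions = 6.0 h fails both > 7.2 and > 6.0 (60% of core); 4 sessions = 8 h passes both. The requirement is 4 of 5 on either base.
- 8 h course: 3 sessions = 6.0 h is 75% of the course. It fails > 6.0 (scaled) and > 7.2 (fixed) but passes > 4.8 (0.6 × 8, core base). The requirement is 4 of 4 now and 3 of 4 on a core base.

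**Weekly arm.** If follow-up hours count and both are attended, the core hours needed are:

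- 10 h course: more than 7.2 − 2 = 5.2 h (52%);
- 8 h course: more than 6.0 − 2 = 4.0 h (50%, scaled) or 7.2 − 2 = 5.2 h (65%, fixed).

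That is up to 2 core hours fewer than the intensive arm needs. If follow-up hours do not count and 7.2 h is a floor, 1 h sessions give 8 of 10 or 8 of 8, against 7 of 10 or 5 of 8 on a core base. The bar is then too high in both arms alike.

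**The case against.** Several points on the other side carry weight.

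- **The 90% figure.** The rule is worded as a proportion, and both intervention sections let hours vary by disorder. It is natural to read 7.2 h as an example that scales. On that reading an 8 h course has a bar of 75%. A reader might infer that the plan demands 90% of an 8 h course; that needs the example to override the rule, and the protocol does not say it does. This stands.
- **The 8 h example is a tie.** On the scaled reading, 6.0 h fails only because it is not more than 6.0 h. Parameter (4) omits that sign, and without it she passes. The same omission would let 3 of 5 sessions pass on a 10 h core base. This also stands.
- **Session length is inferred.** With 8 h in five equal sessions of 1.6 h, the scaled bar and the core bar both need 4 (6.4 h > 6.0; 3 sessions = 4.8 h is not > 4.8). With 10 h in four sessions of 2.5 h, both bases need 3.
- **Unequal treatment of the arms is conditional.** It arises only if follow-up hours count, which the protocol suggests (10 + 2 = 12) but does not state.
- **The threshold may be deliberate.** It carries a citation that is not available here. The text, however, presents 7.2 h as what the 60% rule amounts to, not as a minimum dose in its own right.
- **Follow-ups are part of each intervention as described,** so counting them is defensible in principle. It is not workable for an arm that must earn its hours in 2 weeks.

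None of this brings the intensive bar back to 60%.

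**Conclusion.** Criterion (iii) does not do what it says for the intensive arm. With both follow-ups outside the window, the bar is 72% of a 10 h course and 75% of an 8 h course on the scaled reading, and 90% of the latter only if 7.2 h is a fixed floor. The 2-week condition itself is legitimate; the fault is in the base.

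The practical reach is limited. With 2 h sessions, only women on 8 h courses are classified differently, and on the scaled reading that turns on the 'more than' sign. A reader might infer that the intensive format is set up to miss the 70% criterion. The protocol does not support that: it gives neither the share of 8 h courses nor expected attendance, and on a 10 h course the number of sessions needed does not change. Nor is it established that the weekly arm has an easier rule, since that depends on whether follow-up hours count. The point deserves correction because a stated progression threshold does not match the planned course.

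**What to change.** By dated amendment, define completion in Outcome progression criteria (iii) and in parameter (4) as more than 60% of the core CBT hours planned for the woman's disorder: more than 4.8 h of 8, more than 6.0 h of 10. Apply it to both arms with the same 'more than' sign. Leave follow-up sessions out of numerator and denominator, and keep the 2-week condition for the intensive arm. Report follow-up attendance as a separate line, and show the completion result under the 7.2 h rule alongside. The clinical leads should confirm the planned core hours per disorder.

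No new data should be needed: therapists already record contact time (Measures related to primary objectives) and sessions attended (Strategies to improve adherence to interventions). The assumption is that session dates can be read from the same notes. The change is nevertheless more than editorial. Recruitment began in September 2019, so a progression criterion would be altered in a running trial, which is why it should be dated and both results shown. The downside is that the hours bar becomes lower than the figure now stated, and follow-up attendance no longer counts towards dose.

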### Plans to promote participant retention and complete follow-up

Participants will receive an incentive (£10) for the additional burden incurred from completing assessments at two time points. Participants will receive £10 for participating in the baseline assessment and £10 for participating in final outcome point assessments. They will be encouraged to take part in the final outcome point assessment regardless of treatment completion.

### Sample size estimation

In line with guidance on feasibility studies, no power calculation has been carried out [55]. A sample size of 30 in each intervention group has been recommended to answer questions relating to feasibility [56, 57].

### Data management

The trial statistician will assist with management of the trial data which will be split into 3 databases. The participant main database and therapy database will be stored in separate SPSS files on a network drive only accessible by the CI and trial statistician. The AE (adverse events) database will be stored as a password-protected Excel file on a network drive accessible by the CI only. All databases will be backed up periodically (approx. every 3 months), by creating a date-stamped ZIP file storing all databases and storing in a subfolder titled ‘Archives’. This will be carried out by both the trial statistician and the CI separately.

All research data will be pseudonymised using unique identification numbers and stored without contact details (names or addresses). Associations between participants' contact details and identification numbers will be stored in a separate encrypted electronic password-protected database. Access to this document will be restricted to the Chief Investigator. All data will be held on a secure database on an encrypted, password-protected computer and access to it will be restricted to the research team. Audio files of the qualitative interviews will be retained until they have been transcribed to written form. Transcriptions of qualitative interviews will be completed as soon as possible after collection, anonymised and uploaded to the computer software programme, QSR N-VIVO. Hardcopies of study consent forms held by the central research team will be kept in a locked cabinet at the Institute of Psychiatry, Psychology & Neuroscience and retained for 7 years post research data analysis.

#### Questionnaire data

Questionnaire data will be collected via weblink using existing data collection methods in IAPT services and/or hard copies as preferred, completed in participants own time. Initial clinician interviews will be conducted over the phone at a suitable time for the mother, or in person if she prefers. IAPT measures are routinely collected at each contact so collecting this treatment data will not involve additional burden for women.

All outcomes will be summarized at 3 months postpartum; video and qualitative interview audio data will be collected during a visit to the participant’s home (or remotely) at this point in addition to the IAPT measures.

As per standard practice in IAPT services, anxiety, depression and disorder-specific measures will be taken at each point of contact. Participants will be asked to complete the additional measures at the baseline and outcome points.

#### Video data

All video recordings will be collected using password-protected iPads or via Microsoft Teams. The iPads will be brought back to the university site for secure storage directly after the interview. Video recordings will be immediately uploaded on to the secure university computer network, which is password-protected and which only the research team have access. Once the video recordings have been transferred onto the secure computer network, they will be permanently deleted from the iPads or TEAMS. In order to verify the deletion of the files, we will empty the ‘trash’ file of the iPads. The iPads will be linked to a cloud account in order to be able to wipe them remotely should they be stolen. The video data files will be saved on the secure university computer network using only participant ID and date as identifiers, and only researchers involved in the project will have access to the drive with the video recordings.

### Confidentiality

Participants will be registered as patients under secure local NHS clinical patient records systems (known as IAPTUS) which will hold their personal data. Participants research data (questionnaires) will be pseudonymised and entered on password-protected databases as described above, kept on university computers. Video and audio data will be identified by participants number only. Participants names will be kept in a separate password protected database.

### Statistical methods

#### Quantitative data

Quantitative data analysis will be primarily descriptive to aid the planning of a future RCT. Participant flow through the study will be presented following CONSORT guidelines. Descriptive data will be presented in the form of means and standard deviations; medians and ranges; or percentages with 95% confidence intervals, as appropriate depending on the data being described.

The following feasibility parameters will be calculated: (1) percentage of participants meeting eligibility criteria (those eligible/those approached or referred) by recruitment channel into the study; (2) number of participants recruited per month (defined as those consented); (3) percentage of individuals consenting to randomisation (those randomised/those consented); (4) percentage of participants completing treatment in each arm (number of participants receiving adequate treatment dose, defined as 60% of treatment hours/those randomised); (5) percentage completing the outcome measures at 3m postpartum (number of participants completed at least one follow-up measure/those randomised); (6) between group pre-post effect sizes and confidence intervals, adjusting for randomisation stratifiers (fixed effect) and therapist (random effect), and variance on the potential primary outcome measure at 3 months post-randomisation; (7) summary statistics on acceptability of intervention and outcome measures measured using a 3-point Likert scale. Data will be presented overall and subgroup summaries by disorder.

Descriptive data on therapist competence and compliance will be presented using standardised Cognitive Therapy Scale Ratings (CTS-R) and number of treatment elements completed from checklist.

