### Exclusion criteria

The exclusion criteria are as follows:
Pregnant women with a primary DSM-V depressive disorder, affective or psychotic disorder or current problems with substance abusePregnant women with ‘complex PTSD’ (defined as prolonged multiple traumas affecting a number of domains)Pregnant women who have a medically high-risk pregnancy at the time of recruitment involving significant additional management (e.g. multiple sclerosis, lupus, polycystic ovary syndrome)Pregnant women who are receiving cognitive behaviour therapy or another individual or group psychological therapyPregnant women who are unable to read English adequately to complete questionnaires

The research psychologist will obtain informed consent from potential trial participants who will send a signed consent form. Women will be given at least 24 h after receiving the information sheet to decide whether to proceed with consent and baseline measures. Figure 1 shows the participant timeline through the study.

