### Implementation

The allocation sequence is generated by the KCTU online system. The research psychologist will enrol participants. Once an eligible woman has given consent to participate in the study and completed baseline measures, the research psychologist will use the online system to perform the randomisation. The research psychologist will communicate information about the allocation group to the participant (either time-intensive CBT treatment (IN-CBT) or standard weekly CBT treatment) and to the therapist who will arrange an appointment with the participant at the earliest mutually convenient opportunity.

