### Measures related to secondary objectives

#### Initial clinician interview collected at baseline

*Structured clinical interview for DSM-V* (SCID-V [33];). This semi-structured interview is used by clinicians to establish DSM-V diagnoses, which will be part of initial screening for inclusion in the trial [34].

Routinely collected IAPT data collected at baseline, each clinical session and 3 months postpartum:
*Demographic* (at baseline only)—maternal age, ethnicity, occupation, relationship status, whether they are taking psychotropic medication and pregnancy stage will be recorded.**GAD-7* [35] is a well validated and widely used 7 item measure of anxiety and a key IAPT outcome measure used routinely. A change of 4 or more on the GAD has been found to be clinically significant across anxiety disorders [36]. *This is the potential primary outcome measure for a future evaluation trial.*PHQ-9* [37] is a well-validated 9-item questionnaire used to measure symptoms of depression. It is also a key IAPT outcome measure.The *Work and Social Adjustment Scale* [38] is a 5-item patient self-report measure, which assesses the impact of a person’s mental health difficulties on their ability to function in terms of work, home management, social leisure, private leisure and personal or family relationships.Disorder specific measures: one of the following will be used depending on primary disorder.OCD: Obsessive Compulsive Inventory-Revised (OCI [39];). This is a 42-item self-report inventory concerning symptoms of OCD. The internal consistency for the full scale is high (0.86–0.95). The OCI also shows good discriminative validity and is reliable to measure change in symptoms over time.Panic: Mobility Inventory (alone) [40]. This self-report scale requires respondents to rate avoidance of a range of specific situations over the last week on a scale of 0–4. The inventory has good reliability, validity and sensitivity to change.PTSD: Impact of Events Scale (IES [41]). This is a 22 item self-report scale of symptoms of PTSD. The scale has excellent internal consistency [42].Social Phobia: The Social Phobia Inventory (SPIN [43]) has 17 items and a cut-off score of 19 or above. For each item, respondents rate from 0 to 4 how bothered they have been by the item during the past week. The total score provides a measure of the severity of social phobia and the item has good sensitivity to change.

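### The 70% randomisation criterion is set on eligible women, but the matching feasibility parameter divides by women who have consented

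*Protocol article*

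**What the plan says.** Outcome progression criteria, item (ii), poses the question "If participants are willing to be randomised" and sets the bar: "We require that 70% of eligible participants are randomised to be deemed feasible". The denominator is eligible women. Item (i) of the same list speaks of eligible and of consented participants separately, so the two words are not used interchangeably.

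Statistical methods (Quantitative data) lists the feasibility parameters to be calculated. The third is "3) percentage of individuals consenting to randomisation (those randomised/those consented". The denominator is consented women. None of the listed parameters divides by eligible women; they appear only as the numerator of parameter (1), by recruitment channel.

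Two other places fix the order of events. The paragraph closing the Exclusion criteria section says: "Women will be given at least 24 h after receiving the information sheet to decide whether to proceed with consent and baseline measures". Implementation places randomisation later: "Once an eligible woman has given consent to participate in the study and completed baseline measures, the research psychologist will use the online system" to randomise her.

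**The concern.** Willingness to be randomised is named in Study aims and objectives as part of the primary objective, and criterion (ii) is the test of it. A woman who reads the information sheet and declines, for whatever reason, does so before consent. She counts against the trial under criterion (ii) and is invisible to parameter (3). The bar and the statistic therefore answer different questions. If the calculated parameter is the one held against 70%, the criterion could be reported as met when it was not. If both figures are available and the plan does not say which one decides, the choice could be made after the data are seen, which pre-set progression criteria are meant to prevent.

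**Working it through.** There is no figure of the plan's own to reproduce. The 70% is a chosen bar, and Sample size estimation says that no power calculation was done. The check compares the two definitions.

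**Inputs**
- Bar: 70%, read as at least 70%, on R/E (Outcome progression criteria (ii)).
- Planned statistic: R/C (Quantitative data, parameter (3)).
- R = 60 randomised, from 30 per group (Sample size estimation).
- R/C and C/E: not given. Assumed ranges are 80–100% for R/C and 40–100% for C/E.

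Here E is the number eligible, C the number consented and R the number randomised.

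**Step 1: the link between the two.** If all consenting women are eligible, as Implementation describes,

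R/E = (R/C) × (C/E).

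Parameter (3) keeps the first factor and drops the second.

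**Step 2: illustration with R/C = 95% (assumed).**

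| C/E (assumed) | Parameter (3), R/C | Criterion (ii), R/E | Criterion (ii) met? |
|---|---|---|---|
| 50% | 95% | 0.95 × 0.50 = 47.5% | no |
| 60% | 95% | 0.95 × 0.60 = 57.0% | no |
| 70% | 95% | 0.95 × 0.70 = 66.5% | no |
| 80% | 95% | 0.95 × 0.80 = 76.0% | yes |

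**Step 3: consent rate needed for criterion (ii).** The break-even is C/E = 0.70/(R/C): 87.5% at R/C = 80%, 77.8% at 90%, 73.7% at 95% and 70.0% at 100%. Below these consent rates the two definitions give opposite answers.

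**Step 4: in counts, with R = 60.** 60/0.70 = 85.7. Criterion (ii) is met with 85 eligible women (60/85 = 70.6%) and missed with 86 (60/86 = 69.8%). Parameter (3) falls below 70% only if at least 86 women consented, that is, if 26 or more were lost between consent and randomisation.

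**Step 5: does the recruitment-rate criterion catch the difference?** Item (i) also asks for at least 3 consented participants a month. Trial status gives September 2019 to end September 2021, 25 months at most. Assume 75 consented (75/25 = 3.0 a month), 60 randomised and 125 eligible. The recruitment rate is met, parameter (3) is 60/75 = 80%, and criterion (ii) is 60/125 = 48%.

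**Step 6: if some women consent before the SCID.** Let q be the share of consented women then found ineligible and w the share of the rest who are randomised, so R/C = (1 − q) × w. With w between 90% and 100%, q = 20% gives 72–80% and q = 30% gives 63–70%. Parameter (3) then falls for a reason unrelated to willingness, and eligible women who declined are still not counted.

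**The case against.** The best defence is that the criterion itself is stated on the right denominator, and that the statistics section nowhere says the 70% is applied to parameter (3). The eligible count is already needed for parameter (1), the randomised count is the denominator of parameters (4) and (5), and a CONSORT flow is promised, so randomised/eligible can be derived. This stands as far as it goes: the data will exist. It does not settle which figure is judged, and the parameter written for this purpose uses the other denominator.

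It is also fair that randomised/eligible is not a pure measure of willingness to be randomised. Eligible women may decline because of questionnaires or the home video. It is overall uptake, but it is the quantity that criterion (ii) names.

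Two stronger readings are tempting. A reader might infer that the bar is passed almost automatically, or that parameter (3) cannot detect a failure. The article does not support this. It gives no consent or loss rates, and the order of SCID and consent is unsettled. Implementation has an eligible woman consenting, and the SCID is described as an interview "which will be part of initial screening for inclusion in the trial". Yet Table 1 and its section heading place the SCID at baseline. If consent comes first, parameter (3) could fall below 70% (Step 6).

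A reader might also infer that the inclusion criterion on being available for either format screens out women who refuse randomisation. Its wording is about self-reported availability, and preference is handled separately: Concealment mechanism has it recorded before randomisation.

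**Conclusion.** The inconsistency is explicit: both definitions are stated in full and they differ, so this is not a detail that a condensed article has left to another document. The calculated figure omits eligible women who decline and can exceed 70% when criterion (ii) fails. The direction of that omission follows from the stated order of events. Its size does not, because the documents give no rates. Over the assumed range of R/C from 80% to 100%, the two definitions disagree whenever fewer than 87.5% to 70.0% of eligible women consent. It is not shown that the bar will be passed regardless of the data, or that most eligible women will refuse.

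**What to change.** Redefine parameter (3) as the number randomised divided by the number meeting all eligibility criteria, including those who then decline consent. Give it a 95% CI and state that the 70% bar is judged on it. Report consented/eligible and randomised/consented as separate descriptive steps in the CONSORT flow. State whether the SCID comes before or after consent, so that it is clear when a woman is counted as eligible.

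The cost is mainly wording, since parameter (1) already requires eligible women to be counted by channel. The downside is a less favourable stated rate, and the figure should be described as uptake among eligible women.
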